# Blood pressure control and treatment adherence in hypertensive patients with metabolic syndrome: protocol of a randomized controlled study based on home blood pressure telemonitoring *vs*. conventional management and assessment of psychological determinants of adherence (TELEBPMET Study)

**DOI:** 10.1186/1745-6215-14-22

**Published:** 2013-01-23

**Keywords:** Hypertension, Blood pressure, Home blood pressure telemonitoring, Adherence, Anxiety, Depression, Personality traits

## Abstract

**Background:**

Inadequate blood pressure control and poor adherence to treatment remain among the major limitations in the management of hypertensive patients, particularly of those at high risk of cardiovascular events. Preliminary evidence suggests that home blood pressure telemonitoring (HBPT) might help increasing the chance of achieving blood pressure targets and improve patient’s therapeutic adherence. However, all these potential advantages of HBPT have not yet been fully investigated.

**Methods/design:**

The purpose of this open label, parallel group, randomized, controlled study is to assess whether, in patients with high cardiovascular risk (treated or untreated essential arterial hypertension - both in the office and in ambulatory conditions over 24 h - and metabolic syndrome), long-term (48 weeks) blood pressure control is more effective when based on HBPT and on the feedback to patients by their doctor between visits, or when based exclusively on blood pressure determination during quarterly office visits (conventional management (CM)). A total of 252 patients will be enrolled and randomized to usual care (*n*=84) or HBPT (*n*=168). The primary study endpoint will be the rate of subjects achieving normal daytime ambulatory blood pressure targets (<135/85 mmHg) 24 weeks and 48 weeks after randomization. In addition, the study will assess the psychological determinants of adherence and persistence to drug therapy, through specific psychological tests administered during the course of the study. Other secondary study endpoints will be related to the impact of HBPT on additional clinical and economic outcomes (number of additional medical visits, direct costs of patient management, number of antihypertensive drugs prescribed, level of cardiovascular risk, degree of target organ damage and rate of cardiovascular events, regression of the metabolic syndrome).

**Discussion:**

The TELEBPMET Study will show whether HBPT is effective in improving blood pressure control and related medical and economic outcomes in hypertensive patients with metabolic syndrome. It will also provide a comprehensive understanding of the psychological determinants of medication adherence and blood pressure control of these patients.

**Trial registration:**

Clinical Trials.gov: NCT01541566

## Background

The prevalence of arterial hypertension in the European population is estimated to approximate 20%
[1]. Hypertension is one of the major risk factors for developing cardiovascular diseases such as heart failure, stroke, coronary heart disease, and renal failure, and it is one of the most frequent reasons for access to medical care
[1,2]. Hypertension is also often associated with other cardiovascular risk factors such as obesity, dyslipidemia, impaired glucose tolerance, or diabetes, which give rise to a condition known as metabolic syndrome, affecting one-quarter of the population and increasing by five- to six-fold cardiac morbidity and mortality as compared to healthy individuals
[3-6].

Although numerous studies have shown that antihypertensive treatment may reduce cardiovascular risk and despite availability of several valuable antihypertensive drug options, today, no more than 30% of treated hypertensive patients maintain a satisfactory blood pressure control
[1,7].

This may be caused by many factors, among which poor or complete lack of adherence to treatment prescriptions have been reported to play a major role. Compliance to therapy seems to be related to many factors including the high number of pills to be taken daily, an excessive cost of the available medications, the lack of motivation and poor patient’s involvement in the management of this clinical condition, the long wait in the doctor’s office, the absence of symptoms, the inability of the patient to understand the real long-term consequences of high blood pressure, and finally the psychological and personality traits of the patients
[8].

Different solutions may be adopted in order to improve blood pressure control and patients’ adherence to therapy. An effective organization for a better management of this condition based on new technologies, through which the efficacy of therapy can be monitored, could help patients to get more involved in the daily care of their treatment, and to better cooperate with the physician. One of the methods used to obtain a better therapy adherence and therefore a more effective blood pressure control is now represented by self-measurement of blood pressure at home by automatic electronic devices
[9]. This method represents a valuable alternative to conventional blood pressure measurement by physicians in their offices. Several studies have shown that, compared to office blood pressure measurement, self-measurement of blood pressure at home allows a better control of blood pressure
[10,11] and that the blood pressure assessment so obtained has a superior prognostic value
[12-15]. Home blood pressure may also have some positive effect on therapeutic adherence, though evidence on this aspect is controversial, with some studies showing a clear benefit and others showing no advantage
[16-19]. Lack of definite evidence might be attributed to the limited number of studies performed so far, and to the heterogeneity of the methodologies employed to assess and quantify patients’ compliance with treatment in the different trials
[16-19].

Evidence from randomized studies suggests that home blood pressure telemonitoring (HBPT), defined as home blood pressure monitoring coupled with telematic data transmission to the doctor and real-time feedback on patient’s status, may improve blood pressure control and compliance to treatment, and may help in optimizing the patient’s therapeutic regimen
[20,21].

Although HBPT may in particular be of great advantage for those patients requiring a closer follow-up, as in the case of high-risk hypertensive patients, at the moment it has not yet been clarified whether this approach may actually improve blood pressure control and adherence and persistence to antihypertensive drug treatment also in this category of hypertensive patients.

## Methods

### Study objectives

The study aims at investigating whether in high-risk patients with hypertension and metabolic syndrome, daytime ambulatory blood pressure control over 48 weeks is more effective when based on regular HBPT (intervention group), through monthly automated blood pressure teletransmission and feedback to the patient by the doctor, rather than when based only on periodic measurements made by doctors in their office during quarterly visits (conventional management (CM) control group). The main study endpoint will be the assessment and comparison of the rate of subjects achieving a daytime ambulatory blood pressure normalization (average daytime blood pressure <135/85 mmHg) in the two randomization groups (intervention *vs*. control).

The study will also assess the psychological determinants of adherence and persistence to drug therapy and the influence of HBPT on such psychological factors, as well as the impact of HBPT on additional clinical and economic outcomes. These will include the number of additional medical visits, direct costs of patient management, number of drugs or drug combinations used to achieve blood pressure control, the level of cardiovascular risk, the degree of target organ damage and frequency of cardiovascular events, and the regression of the metabolic syndrome.

### Study design

The study has an open label, parallel group, randomized, controlled design. After 1 week of run-in, patients will be randomized to two different arms: (1) intervention group (HBPT), with automated teletransmission of home blood pressure values to the Investigator, every month, over the first 24 weeks, followed by manual transmission of self-measured blood pressure data to the HBPT center immediately before each office visit, with regular doctor’s visit every 3 months, in the second 24 weeks (see below for details); (2) control group (CM) managed only through regular office visit every 3 months. A flow chart of the study design is reported in Figure 
1.

**Figure 1 F1:**
[figure not shown]
**Flow chart of the TELEBPMET study design.** ATP, Adult Treatment Panel; BP, Blood pressure; CM, Conventional management; HBPT, Home blood pressure telemonitoring; W, Week.

### Study sites and population

This is an Italian, multicenter trial involving 12 Hypertension Centers, of which seven are located in northern Italy, two in central Italy, and three in southern Italy. The study will be conducted according to Good Clinical Practice guidelines and the Declaration of Helsinki. The protocol will be approved by the Ethics Committees of the centers involved.

The study will include hypertensive patients with metabolic syndrome, who are at an increased risk of cardiovascular events in the short term, and for whom adequate blood pressure control and treatment adherence are clinically relevant issues.

In order to be eligible for inclusion in the study the patients have to comply with the following criteria: (1) male or female gender and age between 18 and 74 years; (2) untreated or treated, but uncontrolled, essential arterial hypertension (office systolic blood pressure ≥140 mmHg and/or diastolic blood pressure ≥90 mm mmHg plus average daytime ambulatory systolic blood pressure ≥135 mmHg and/or average daytime diastolic blood pressure ≥85 mm Hg); (3) presence of metabolic syndrome according to ATP-III criteria
[22], namely occurrence of at least two of the following four clinical conditions: abdominal obesity (waist circumference ≥102 cm in men and ≥88 cm in women), raised triglycerides (≥150 mg/dL or under specific treatment with fibrates or nicotinic acid), reduced HDL cholesterol (<40 mg/dL in men and <50 mg/dL in women or under specific treatment with fibrates or nicotinic acid), elevated fasting glucose (≥100 mg/dL or use of medication for hyperglycemia).

Main exclusion criteria are: (1) secondary hypertension; (2) renal or liver impairment; (3) severe autoimmune diseases; (4) neoplasia; (5) atrial fibrillation, frequent ectopic beats or severe conduction disturbances (second and third degree atrio-ventricular block), which may make automatic blood pressure measurement difficult or unreliable; (6) an arm circumference >32 cm or <22 cm; (7) any other condition that might compromise the patient’s participation in the study, including illiteracy and diseases preventing the completion of questionnaires (for example, myopia); (8) patients not able to follow study procedures.

Patients meeting inclusion criteria will be fully informed about the study design and purposes and asked to give a written informed consent, if willing to participate. After obtaining the written informed consent, eligible patients will be randomized to one of the two study arms.

### Randomization

Randomization will be performed using a blocked randomization procedure (computerized random numbers), in order to obtain equal numbers in each study arm. Patients will be randomized to CM or HBPT (1:2). In order to prevent selection bias, the allocation sequence will be concealed from the Investigator enrolling and assessing patients in sequentially numbered, opaque, and sealed envelopes.

### Description of the intervention: HBPT

At the time of the randomization, patients assigned to HBPT, will be equipped with an electronic blood pressure measuring device and a wireless transmitting interface. These devices will be kept at home until the end of the study.

The patient will be adequately trained by the Investigator on measurement procedures. Patients will be asked to self-measure their blood pressure at home twice a day, using a validated, automatic, electronic, oscillometric, upper arm monitor (A&D UA-767PC, A&D Company Ltd., Tokyo, Japan)
[23]. The device can store up to 126 blood pressure measurements in its memory, is operated by non-rechargeable batteries, and is equipped with a serial port for interfacing with a personal computer or a transmission unit.

Two measurements, at a 2-min interval, will be taken in the morning before going to work or before starting daily activities (between 08:00 and 10:00), and two measurements will be taken in the evening (between 18:00 and 22:00), for a minimum of 3 days a week. The measurements have to be taken in a quiet environment, with the patient in a relaxed, comfortable, sitting position for at least 5 min before self-measurement.

After each measuring session and when not used for measuring blood pressure, the blood pressure monitor will be connected through a serial cable to a GPRS wireless interface (BluMed). During the first 24 weeks, the transmitter will send blood pressure data every day to the
http://www.morepress.net website, (Biotechmed Ltd., Somma Lombardo, Varese, Italy) where they will be analyzed and a report will be generated and sent once a month via email to the Investigator. A feedback on the status of patient’s blood pressure control will also be visualized on the interface display.

The wireless interface also comes with a button which allows the patient to manually send the data to the HBPT center whenever it is deemed necessary (for example, in case of symptoms or very high blood pressure values), independently from the scheduled program. During the last 24 weeks of the follow-up no automatic data transmission will be done, but the patient will be requested to manually send to the HBPT center the self-measured blood pressure data, immediately before each scheduled office visit.

A diagram of the telemonitoring web-based system is shown in Figure 
2.

**Figure 2 F2:**
[figure not shown]
**The Morepress web**-**based telemedicine system used in the TELEBPMET Study.** GPRS, General Packet Radio Service; HBPT, Home blood pressure telemonitoring; SSL, Secure Sockets Layer.

### Description of the control condition

In the CM or control group, blood pressure will be measured only during the office visit by the same automatic device used by patients of the HBPT randomization group. After 5 min sitting, automated blood pressure measurements will be performed twice at a 2-min interval and the average of the measurements will be calculated and used as clinical reference.

### Study procedures

Besides baseline screening and randomization visits (Visit 1 and 2), all the patients will be re-assessed at 4 weeks (Visit 3), 12 weeks (Visit 4), 24 weeks (Visit 5), 36 weeks (Visit 6), and 48 weeks (Visit 7) of follow-up. If the Investigator deems it appropriate extra visits can be planned. Figure 
3 presents an overview of variables measured at each time point of the study. All data collected during the study will be entered manually by the Investigator in a web-based electronic case report form (e-CRF) linked to the telemedicine system.

**Figure 3 F3:**
[figure not shown]
**Timing and content of study assessments.** ABPM, Ambulatory blood pressure monitoring; BP, Blood pressure; HBPT, Home blood pressure telemonitoring.

The study includes a first visit at the Hypertension Center (Visit 1) where automatic office blood pressure is measured, the patient’s history gathered, a physical examination performed. Laboratory tests useful for the determination of the organ damage and cardiovascular risk will be assessed as well. These tests include biochemistry and urinalysis (plasma lipids, fasting glucose, glycosylated hemoglobin, creatinine, C-reactive protein, albumin/creatinine ratio on morning urine sample or 24-h microalbuminuria), an echocardiogram with determination of left ventricular mass, a carotid ultrasonography for determination of intima-media thickness, a fundoscopy, and an electrocardiogram (ECG). Waist circumference will also be measured. A 24-h ambulatory blood pressure monitoring will be performed (see below for details).

Within 1 week from Visit 1 those patients complying with the inclusion criteria (that is, values of office systolic blood pressure ≥140 mmHg and/or office diastolic blood pressure ≥90 mmHg plus daytime systolic blood pressure ≥135 and/or daytime diastolic blood pressure ≥85 mmHg, plus presence of metabolic syndrome) will be randomized to the CM group or to the HBPT group (Visit 2).

During the same visit the patients will be administered the following psychological tests: Medical Outcome Survey Short-Form 36 (SF-36), Psychological General Well-Being Index (PGWBI), Beck Depression Inventory (BDI), Locus of Control (LoC), Self-Esteem Inventory (SEI), Illness Behaviour Questionnaire (IBQ) and Coping strategies (COPE), forming set 1, and Trait Anxiety Inventory (STAY), Type D Personality (TDP), Type A Personality (TAP), Temperament and Character Inventory (TCI), forming set 2
[24-35]. In untreated patients an antihypertensive treatment will be initiated. In treated patients, antihypertensive drug treatment will be adjusted in order to improve blood pressure control and possibly achieve office blood pressure normalization (<140/90 mmHg) on the next visit.

Four weeks later (Visit 3) the patients will be visited again by the Investigator and the medical therapy will be adjusted on the basis of office blood pressure (target, <140/90 mmHg) in the CM group or home blood pressure (target, <135/85 mmHg) in the HBPT group. Office blood pressure will still be measured by the Investigator with the same automatic electronic instrument used for self-measurement, in all patients, including those randomized to HBPT. Additional visits are scheduled 12, 24, 36, and 48 weeks after randomization (Visits 4, 5, 6, and 7). During each of these visits office blood pressure will be measured and antihypertensive medication will be changed according to office (CM group) or home blood pressure values (HBPT group). Drug treatment can also be changed in the patients of the HBPT between the scheduled visits, based on the home blood pressure report monthly received and reviewed by the Investigator. The same laboratory tests performed at screening visit and a 24-h ambulatory blood pressure recording will be repeated at Visits 5 and 7. During these two visits psychological tests will also be administered, with the exclusion of STAY, TDP, TAP, and TCI test, administered only at Visit 2.

Occurrence of adverse events, adherence to therapy and concomitant therapies will be checked at all visits during the trial. Evaluation of adherence to drug treatment will be based on patient’s report on amount of prescribed drug intake and on counting the quantity of study medication taken by the patient, comparing this datum with the quantity expected to be returned. The Investigator will instruct each patient to bring back used and unused drug blisters at each visit. The compliance will be computed as the ratio between the number of pills taken and the number of pills which should have been taken, expressed as a percentage, and will then be graded as follows: excellent (100% of prescribed pills taken), good (80% to 99%), fair (40% to 79%), or poor (<40%).

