### Home blood pressure monitoring

The modality of self-blood pressure measurement at home has been detailed in the previous sections. In the HBPT group home blood pressure reports will be automatically transmitted to the Investigator every month for the first 12 weeks (from Visits 2 to 5). Based on these reports, the Investigator will be allowed to adjust drug treatment before the next visit or to schedule an extra study visit. Starting from Visit 5 until the end of the study (Visit 7), the patients randomized to HBPT will continue to self-measure blood pressure at home, but automatic transmission will be disabled and each patient will be asked to manually send blood pressure data the day immediately preceding the office visit at the Center. These home blood pressure measurements will be reviewed by the Investigator exclusively on Visits 6 and 7, and treatment adjusted accordingly.

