#### Planned statistical analyses

Analysis will be performed on patients valid for intention-to-treat, defined as all subjects with at least one visit during the randomized phase of the study and with valid ambulatory blood pressure recordings at baseline, after 24 and 48 weeks of follow-up even in the presence of protocol violations. A confirmatory analysis on the per-protocol (patients who have successfully completed the study without major protocol violations) is also foreseen.

The demographic and clinical characteristics of the two study groups will be compared at baseline by analysis of variance (continuous variables) or by Mantel-Haenszel Chi-square test (categorical variables), in order to verify the between-group homogeneity at randomization. The same tests will be used to compare primary and secondary study endpoints between the CM and HBPT groups. If deemed necessary, in addition to the univariate approaches, multivariate analysis methods will be used.

The type and frequency of drug-related adverse events will be reported for each randomization group. The absolute rate of adverse events will be compared between groups using the Chi-square test.

The minimum level of statistical significance will be set at *P* <0.05.

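### The between-arm adverse-event comparison is open to unequal ascertainment, because only the HBPT arm has a report-driven route to extra visits; bias is possible but not demonstrated

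*Protocol article*

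**What the plan says.** Study procedures gives both arms the same follow-up visits, at weeks 4, 12, 24, 36 and 48 (Visits 3 to 7), and adds for any patient: "If the Investigator deems it appropriate extra visits can be planned". On safety collection, the visit description under the timing-of-assessments figure says: "Occurrence of adverse events, adherence to therapy and concomitant therapies will be checked at all visits during the trial". Nothing limits this to scheduled visits.

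The arms differ in what happens between visits. Study design describes a "control group (CM) managed only through regular office visit every 3 months". For HBPT, Home blood pressure monitoring says: "Based on these reports, the Investigator will be allowed to adjust drug treatment before the next visit or to schedule an extra study visit". The visit description adds: "Drug treatment can also be changed in the patients of the HBPT between the scheduled visits". From Visit 5 onward automatic transmission is switched off, and the Investigator reviews home data only at Visits 6 and 7.

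Planned statistical analyses then fixes the test: "The absolute rate of adverse events will be compared between groups using the Chi-square test". The design is open label.

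**The concern.** An event that is asked about soon after it happens is more likely to be recorded than one asked about weeks later. In HBPT, a monthly report may lead to an extra study visit, and on the plain reading of the rule adverse events are checked there too. CM patients have no report to prompt such a visit. With identical true risk, HBPT could therefore show more recorded events in the first 24 weeks simply because those patients were asked more often and over shorter recall periods.

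What is at stake is how a safety difference is read. Report-driven drug changes in HBPT could also produce a real difference in adverse events. A chi-square test over all contacts cannot tell that effect of the strategy from more frequent asking.

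**Working it through.** The documents state no adverse-event rate, extra-visit rate or recall figure, so there is no figure of the plan to reproduce. What follows is a what-if calculation.

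**Inputs from the protocol article.** Scheduled contacts in both arms at weeks 4, 12, 24, 36, 48; monthly reports in HBPT to week 24; 84 CM and 168 HBPT patients; two-sided 5% test. Reports at weeks 4, 12 and 24 coincide with visits, so the possible extra contacts are at weeks 8, 16 and 20. (Home blood pressure monitoring gives the reporting period as 12 weeks but also as Visits 2 to 5, and Visit 5 is week 24. Study design says 24 weeks, used here; a shorter period would reduce the effect.)

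**Assumptions.** No extra visits in CM; all patients followed for 48 weeks; equal true risk of r = 0.5 to 1 event per patient-year, Poisson; the chance of recording an event halves every h = 4, 8 or 12 weeks until the next contact; the rate tested is the proportion of patients with at least one recorded event.

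**Step 1, mean delay to the next contact**, Σ L²/(2 × 24) over intervals of length L, if every report triggers a contact:
- Weeks 0-24, CM: (4² + 8² + 12²)/48 = 224/48 = 4.7 weeks.
- Weeks 0-24, HBPT: 6 × 4²/48 = 2.0 weeks.
- Weeks 24-48, both arms: 2 × 12²/48 = 6.0 weeks.

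**Step 2, share of events captured**, (h/ln 2) × Σ(1 − 0.5^(L/h))/24:

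| h (weeks) | CM, weeks 0-24 | HBPT, weeks 0-24 | Both, weeks 24-48 |
|---|---|---|---|
| 4 | 0.51 | 0.72 | 0.42 |
| 8 | 0.69 | 0.85 | 0.62 |
| 12 | 0.78 | 0.89 | 0.72 |

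**Step 3, proportion with a recorded event**, p = 1 − exp[−r × (24/52) × (share in weeks 0-24 + share in weeks 24-48)]. For r = 1 and h = 4, CM is 1 − exp(−0.430) = 0.350 and HBPT is 1 − exp(−0.527) = 0.410, a difference d = 0.0602.

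**Step 4, false rejection.** With s0 the pooled and s1 the unpooled standard error, P = 1 − Φ[(1.96 s0 − d)/s1] + Φ[(−1.96 s0 − d)/s1]. In the same case s0 = 0.0652 and s1 = 0.0644. The first part is 1 − Φ(1.05) = 0.147 and the total is 0.149.

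**Step 5, vary the share of reports that lead to a contact**, each report triggering independently and the captured share averaged over the eight possible patterns:

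| Reports leading to a contact | r = 0.5; h = 4 / 8 / 12 | r = 1; h = 4 / 8 / 12 |
|---|---|---|
| All | 10.1 / 6.9 / 5.9% | 14.9 / 8.6 / 6.8% |
| Half | 6.4 / 5.5 / 5.3% | 7.9 / 6.1 / 5.6% |
| A quarter | 5.3 / 5.1 / 5.1% | 5.7 / 5.3 / 5.2% |
| One in ten | 5.0 / 5.0 / 5.0% | 5.1 / 5.0 / 5.0% |

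The excess over 5% falls faster than the trigger share: in the worst case it goes from 9.9 points to 2.9 to 0.7. It lies on one side. False findings against HBPT, nominally 2.5%, are 4.8-14.7% if all reports trigger a contact, 3.6-7.2% if half do, and 3.0-4.5% if a quarter do.

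**Cross-check without a recall model.** Assume true event proportions of 10-40% and set detection directly. Detection of 0.90 in CM against 0.95 in HBPT gives a false finding against HBPT in 3.2-4.9% of trials; 0.80 against 0.90 gives 4.2-8.9%; 0.70 against 0.90 gives 7-24%. Equal detection gives 2.5%.

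**The case against.** A reader might infer that the comparison is biased against HBPT. The documents do not support that. Both arms have the same five visits with adverse-event checks, so an event between visits is lost in CM only if it is forgotten or goes unreported at the next one. If scheduled visits recover events equally, the bias is zero. Extra visits are also open to CM patients; only the home-report trigger belongs to HBPT alone. That trigger is permissive: the Investigator may change treatment or schedule a visit, and a report on a controlled patient calls for neither. Laboratory tests are repeated at Visits 5 and 7 in both arms, so findings from them do not rest on recall. All of this stands, and it is why the every-report row is an upper case.

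A reader might also take a fall in HBPT events after week 24 as the signature of ascertainment. It is not, because report-driven drug changes stop at the same visit as the reports.

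It can be said, too, that reporting all events is a defensible choice, that the number of office or phone visits is already a secondary endpoint and would reveal unequal contact, and that refinements belong in the analysis plan. The first two points stand, but visit counts do not correct the test. The third only partly stands: the article itself fixes both the collection rule and the test, and together they leave the opportunity to record events unequal.

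**Conclusion.** The point holds as a risk. Collecting events at all visits, giving one arm alone a report-driven route to extra visits, and comparing rates over all contacts in an open-label trial leaves the comparison open to differential ascertainment. The likely direction is more recorded events in HBPT.

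The size rests entirely on the assumed recall half-life, event rate and trigger share. The inflation is material only if extra visits after reports are common; at a quarter of reports or fewer the two-sided rejection rate is close to nominal. The point is of low priority and does not touch the primary endpoint.

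**What to change.** Flag each adverse event in the e-CRF as first recorded at a scheduled or an extra contact. At Visits 3 to 7, ask both arms the same question, covering the whole time since the last scheduled visit and including anything already mentioned at an extra contact. Base an ascertainment-balanced comparison on the events so elicited, show it beside the all-event comparison, and tabulate events first recorded at extra contacts by arm. If results are shown by period, state that a contrast of weeks 0-24 with weeks 24-48 does not isolate ascertainment. The two statements of the automatic reporting period (12 weeks, and Visits 2 to 5) should be reconciled, because they set the window in which the arms differ.

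The cost is one e-CRF field, a standard question and a few sentences of analysis text; no safety data are lost. The restricted comparison may hold somewhat fewer events, and some priming will remain, since an event discussed at an extra visit is more easily recalled at the next scheduled one. Trial status says that follow-up is already under way, so the common question can apply only from its introduction; the flag could be filled in retrospectively if the date and type of each contact were kept.
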